### Relevant concomitant care permitted or prohibited during the trial {11d}

During the trial, any drugs (including antibiotics, parasympathetic inhibitors, muscle relaxants, opiates, other probiotics, antidepressants, anti-anxiety drugs, and Chinese traditional medicine) or other external therapies (including acupuncture, electro-acupuncture, and electric stimulation) that may have impact on the evaluation of the effectiveness of *Bifidobacterium* quadruple viable tablet affecting abdominal pain and diarrhea are not allowed. Drugs that have been used before baseline which are not opposite to the requirement of treatment or forbidden in the exclusion criteria will be permitted during the trial.

### Provisions for post-trial care {30}

There is no anticipated harm and compensation for trial participation.

### Outcomes {12}

#### Primary outcome measures

The primary outcome of this trial is the response rate. A patient is categorized as a responder if the patient is a responder in both pain intensity and stool consistency. The strength of abdominal pain will be evaluated by numerical rating scale using 0 to 10 to represent different levels of pain: 0 means no pain and 10 means severe pain (unable to perform activities of daily living). The consistency of stool will be assessed by using the Bristol Stool Form Scale (BSFS), classified into seven categories:
Type 1: Separate hard lumps, like nuts (hard to pass)Type 2: Sausage-shaped, but lumpyType 3: Like a sausage but with cracks on its surfaceType 4: Like a sausage or snake, smooth and softType 5: Soft blobs with clear cut edges (easy to pass)Type 6: Fluffy pieces with ragged edges, a mushy stoolType 7: Watery, no solid pieces, entirely liquid

The treatment will be considered effective when two criteria are reached simultaneously.

##### Effective in improving abdominal pain for 4 weeks

It will be regarded as remission of abdominal pain for a week when the average of the highest scores of abdominal pain everyday within the week after treatment decreases by more than 30% compared with the week before the treatment. And it will be regarded as the effectiveness of drugs in improving abdominal pain when the remission of abdominal pain lasts for more than half of the treatment period (≥ 2 weeks).

##### Effective in improving stool consistency for 4 weeks

It will be regarded as improvement of stool consistency for a week when the number of days with type 6 or 7 feces within the week after treatment decreases by more than 50% compared with the screening period. And it will be regarded as the effectiveness of drugs in improving stool consistency when the improvement of stool consistency lasts for more than half of the treatment period (≥ 2 weeks).

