### Trial design {8}

This study is a parallel, double-blind, placebo-controlled, multicenter randomized controlled trial (RCT). The trial will include three periods: a 2-week screening period, a 4-week treatment period, and a 2-week follow-up period. During the screening period, patients will record a symptom diary every day including abdominal pain intensity, stool consistency, evaluation of symptom remission, and the changes in the pattern of bowel movement. Those who record all items in the symptom diary for at least 10 days during the screening period and fulfill the eligibility criteria will be randomized at a ratio of 1:1 into either the *Bifidobacterium* quadruple viable tablet group or the placebo group. The time schedule and outcome assessment of the trial are presented in Figs. 1 and 2.

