### Eligibility criteria {10}

#### Inclusion criteria

Patients participated voluntarily and signed informed consent.Aged 18–65 years old.Patients were diagnosed as diarrhea predominant irritable bowel syndrome (IBS-D) by Drossman 2016 [22].After 2 weeks of screening (7 days before the beginning of treatment), patients have abdominal pain at least 2 days a week, and the mean value of the most severe abdominal pain was more than 3 (11—NRS report). Meanwhile, the fecal traits were classified as type 6 or 7 at least 2 days.During the screening period (14 ± 3 days before the onset of treatment), the patients completed the symptom diary for at least 10 days.Patients discontinued the drugs used in the pre-screening stage for abdominal symptoms or diarrhea.The lifestyle during the visit (from the first visit before screening to the last visit of the trial) did not make any significant changes in the symptoms of diarrhea and abdominal pain (for example, starting a new diet, or changing the usual exercise pattern).Colonoscopy report within 2 years of tertiary hospitals in China was normal, or the researchers considered no clinical significance (such as chronic colitis diagnosed by congestion and edema, but no erosive ulcer; the diameter of colonic polyps was less than 3 mm, and the number was less than 5).

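### Read literally, the stool half of the primary endpoint sets a 7-day count against an unscaled count from a screening period of about 14 days, so window length alone can produce a stool response

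*Protocol article*

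**What the plan says.** The primary outcome is a composite: "A patient is categorized as a responder if the patient is a responder in both pain intensity and stool consistency".

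For stool, a week counts as improved on this condition: "number of days with type 6 or 7 feces within the week after treatment decreases by more than 50% compared with the screening period". The patient is a stool responder when "improvement of stool consistency lasts for more than half of the treatment period (≥ 2 weeks").

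For pain, a week counts as remission when the average of the daily worst scores "decreases by more than 30% compared with the week before the treatment".

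The Trial design section describes "a 2-week screening period, a 4-week treatment period, and a 2-week follow-up period". The inclusion criteria give the tolerance and the minimum diary: "During the screening period (14 ± 3 days before the onset of treatment), the patients completed the symptom diary for at least 10 days". The Participant timeline section repeats the ± 3 days. The entry criterion for pain and stool carries its own window, "After 2 weeks of screening (7 days before the beginning of treatment"), and then adds "Meanwhile, the fecal traits were classified as type 6 or 7 at least 2 days".

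**The concern.** The stool rule compares counts of days. Its treatment side covers 7 days. Its baseline side is a named period that lasts 11 to 17 days, and nothing in the article divides that count down to a week. Elsewhere the article names one week when it wants one: for the pain baseline and, apparently, for entry. The two halves of the composite therefore have different baselines. Pain uses an average, which tolerates windows of unequal length; stool uses a count, which does not.

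If the sentence is programmed as it stands, part or all of the required halving comes from the calendar. Patients whose stools have not changed can pass, and whether they pass depends on how long screening lasted and how many diary pages were completed.

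**Working it through.** **The plan's own figure.** The article gives no number for the stool rule itself. The nearest stated figure is the sample size, and it reproduces: n = [1.960·√(2·0.4·0.6) + 1.282·√(0.5·0.5 + 0.3·0.7)]² / 0.2² = (1.358 + 0.869)² / 0.04 ≈ 124 per group. It rests on assumed composite rates of 50% and 30%, so it does not change with the stool definition.

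**Step 1: window length alone.** Let S be the number of screening days counted, B the type 6/7 days in them, and W the type 6/7 days in one treatment week. With an unchanged daily rate the expected W/B is 7/S:
- S = 11: 7/11 = 0.636, a fall of 36%
- S = 14: 7/14 = 0.500, a fall of 50%
- S = 17: 7/17 = 0.412, a fall of 59%

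**Step 2: the real change needed.** Improvement requires W < 0.5·B. As daily rates, (W/7)/(B/S) must be below 0.5·S/7:
- S = 10: 0.714, so the rate must fall by more than 29%
- S = 11: 0.786, more than 21%
- S = 14: 1.000, any fall
- S = 17: 1.214, so even a rise of up to 21% passes

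The extreme case needs no model. A patient with loose stools every day and no change has W = 7. At 14 days the limit is W < 7 and the patient fails every week. At 15 days the limit is W < 7.5 and the patient passes every week.

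**Step 3: unchanged patients classed as stool responders.** Assumptions: daily probability p of a type 6/7 day is the same in screening and treatment; days are independent; diaries are complete over the S days; at least 2 such days fall in the last 7 screening days (the entry rule). The documents give no p, so a range is shown. For each baseline count B, q(B) = P[Bin(7, p) < 0.5·B]. The chance of response is P[Bin(4, q(B)) ≥ 2], averaged over the distribution of B. Exact results:

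| Baseline | p = 0.3 | 0.4 | 0.5 | 0.6 | 0.7 | 0.8 | 0.9 |
|---|---|---|---|---|---|---|---|
| 10 diary days, raw count | 45% | 33% | 24% | 17% | 11% | 4% | 0.3% |
| 11 days, raw count | 51% | 40% | 32% | 26% | 19% | 11% | 4% |
| 14 days, raw count | 67% | 61% | 57% | 55% | 53% | 50% | 46% |
| 17 days, raw count | 79% | 78% | 78% | 79% | 82% | 86% | 92% |
| Last 7 days | 25% | 14% | 7% | 3% | 0.9% | 0.1% | 0.0% |

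A 14-day count scaled to 7 days gives nearly the same as the last row (25% down to 0.0%).

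**Step 4: sensitivity.**
- If 3 of 4 weeks are required, the 14-day row becomes 41, 36, 32, 30, 29, 27 and 21%; the 7-day baseline gives 8% or less.
- With day-to-day correlation of 0.3 to 0.6 and p from 0.4 to 0.8, the raw count gives 18–64% at 11 days, 47–72% at 14 and 74–80% at 17. The 7-day baseline gives 2–48% under the same correlation, so the gap narrows but remains.
- At 14 days the figure drops for patients who are loose almost daily: 30% at p = 0.95 and 0% at p = 1.

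**Step 5: discrimination, as an illustration only.** Assume mean cuts in daily probability of 30% on placebo and 50% on active (patient SD 0.25, limited to 0–100%), with p drawn from Beta(3,2) or Beta(6,4). Stool response, placebo against active, is about 34% against 57% with a 7-day baseline. With the raw count it is 66% against 83% at 11 days, 84% against 93% at 14, and 94% against 98% at 17. The difference between arms shrinks from about 22 points to about 17, 9 and 4. These effects are assumptions, not figures from the article.

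**The case against.** The best defence is that the sentence never says total or whole. It defines a weekly measure, so a weekly rate, or the 7 qualifying days, could be what is meant; the inclusion criteria attach a 7-day window to the same stool count. The full protocol or analysis plan may fix the derivation. This stands in part: the raw count is the literal reading, not the only one. But a programmer would have to choose among a raw count, half of it, a rate per recorded day, or the last 7 days. The raw count, at least, classes patients very differently from the rest, so the sentence needs correcting on any reading.

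Several stronger conclusions are tempting, and the documents do not support them:
- **Half or more of unchanged patients respond whatever the screening length.** This is about right at 14 days and clearly so at 17. It fails at 11 days (4–51%) and with 10 diary days (0.3–45%).
- **Almost no real improvement is ever needed.** With 10 or 11 days a fall of more than 29% or 21% is still required.
- **False positive trial results.** A stool response alone does not make a primary responder, and the same rule applies to both blinded arms, so type I error is not raised.
- **The composite collapses to a pain endpoint, or the planning rates are void.** No composite rate can be derived without the joint behaviour of pain and stool, which the article does not give. The 50% and 30% come from a review of overall symptom relief combined with clinical experience, not from this definition.
- **The longer window captures drug washout.** The inclusion criteria say earlier symptom drugs were discontinued but give no date.

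**Conclusion.** The point holds as a defect in a stated primary-endpoint rule. The stool baseline is unscaled as written, differs from the pain baseline and the entry window, and, followed literally, classes many unchanged patients as stool responders: 46–67% at the nominal 14 days, 4–51% at 11 and about 78–92% at 17, against 0–25% with a 7-day baseline. These figures rest on the literal raw-count reading, an assumed daily probability of 0.3 to 0.9, independent days, complete diaries and the 2-of-4-weeks rule. Requiring 3 of 4 weeks lowers the 14-day range to 21–41%. The window arithmetic in Steps 1 and 2 does not depend on the daily probability.

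The consequence is a stool component that separates the arms less well, and a responder status that shifts with visit timing and diary completeness. The effect on the power of the composite is not established.

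**What to change.** In the stool criterion, make the comparator the 7 days before treatment, the same baseline week as for pain. Express both sides as the share of recorded days with type 6 or 7 stool, so that missed diary days do not move the threshold. If the sponsor prefers the whole screening period as baseline, compare daily proportions and not raw counts.

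In the same sentence group, reconcile the two statements of duration: more than half of 4 weeks means at least 3, while the parenthesis says 2 or more. The pain criterion has the same conflict and should be settled in the same way.

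The cost is one or two sentences in the protocol or analysis plan and a change to the derivation program, best made before unblinding. No new data are needed, because the daily diary already holds them. The downside is that observed stool response rates will be lower in both arms than under the literal rule.

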#### Secondary outcome measures

##### Evaluation of overall symptom relief

Using 1–7 to represents different levels of overall symptom relief at last 7 days:
complete remissionobvious improvementslightly reliefno changeslightly worseobvious exacerbationthe worst condition imaginable

##### Frequency of defecation

once per daytwice per daythree times per daymore than three times per day

##### Bloating (with borborygmus, increasing passing gas, or belching frequently)

not at allbarelya littlemoderaterather seriousvery seriousunbearable

##### Urgency of defecation

no urgency (feel no need to defecate when it comes to mind)slightly urgent (wish to defecate but not necessarily when it comes to mind)rather urgent (desire to defecate but not immediately)very urgent (have to rush to the bathroom at once)

##### Reduction in BSFS

A reduction of BSFS by three or more points would be adopted as a quantitative indicator to assess the improvement of stool consistency.

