### Sample size {14}

Sample size calculation was performed by using PASS 13. The 4-week treatment effective rate would be adopted as the main evaluation indicator. According to the systematic review published by Zhang et al. [23], when overall symptom relief is regarded as the main evaluation indicator, the effective rate of probiotics was 50% while placebo was 30% in IBS-intervened RCTs. On this basis and combined with clinical experience, it was assumed that the 4-week treatment effective rate of the experimental group was 50% and that of the placebo group was 30%. In the case of *α* = 0.05 and the power of test was 90% (*β* = 0.10), the required sample size would be at least 124 pairs. Considering the certain shedding and withdrawal samples (52 patients), the planned sample size would be 150 cases/group, and the total would be 300 cases (into a 1:1 ratio).

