## Statistical methods

### Statistical methods for primary and secondary outcomes {20a}

#### General analysis

Statistical analysis will be performed by using the SAS 9.4 (or updated version) software (SAS Institute Inc., Cary, NC, USA). In terms of data description, quantitative data will be presented as mean ± standard deviation, median, minimum, maximum, lower quartile (Q1), and upper quartile (Q3), respectively. The categorical data will be presented as frequency and percentage. The comparison of the two groups will be analyzed in proper methods according to the type of indicators. The quantitative data from the two groups will be compared on the basis of data distribution (variance homogeneity, normal distribution) using group *t* test or Wilcoxon’s rank-sum test. A chi-square test or Fisher’s exact test (if the chi-square test is not applicable) will be applied on the categorical data, and Wilcoxon’s rank-sum test or CMH-*χ*^2^ test for the ranked data. Two-sided tests will be applied in all statistical tests, and a *P* value equal to or less than 0.05 will be considered statistically significant (except for special instructions).

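### The secondary stool indicator (BSFS fall of three or more points, no target range or lower limit) fails a change from type 6 to type 4 but credits a fall to type 1

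*Protocol article*

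**What the plan says.** The section Reduction in BSFS consists of one rule: "A reduction of BSFS by three or more points would be adopted as a quantitative indicator to assess the improvement of stool consistency". It does not say whether the fall is counted per stool, per day or on an average, and it gives no range in which the stool should end.

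The scale is set out under Primary outcome measures. It begins with "Type 1: Separate hard lumps, like nuts (hard to pass" and rises through type 4 (formed, smooth, soft) to type 6 (mushy) and type 7 (entirely liquid).

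For entry, the inclusion criteria ask that "the fecal traits were classified as type 6 or 7 at least 2 days". The primary stool criterion uses the same scale differently. A week counts as improved under this condition: "the number of days with type 6 or 7 feces within the week after treatment decreases by more than 50% compared with the screening period". This must hold for at least 2 weeks of the 4-week treatment period.

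**The concern.** The two ends of this scale describe opposite problems, so a lower score is not better all the way down. A rule that rewards any large enough fall, wherever it ends, can treat a well-formed stool as failure and a hard one as success. Patients whose loose stools are mostly type 6 are the ones exposed, because the distance from 6 to 4 is shorter than the threshold.

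At stake is how a secondary result can be read. A real shift from mushy to formed stools could go uncounted, and a shift to hard stools would be reported as better consistency. The article would then carry two measures of stool improvement that disagree in the same patient, with no reason given for the difference.

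**Working it through.** **The plan's own figure.** The indicator has no figure of its own. The sample size rests on the primary response rate: 50% against 30%, alpha 0.05 two-sided, power 90%. With a pooled variance under the null,

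n = [1.960·√(2·0.4·0.6) + 1.2816·√(0.5·0.5 + 0.3·0.7)]² / 0.2² = (1.358 + 0.869)² / 0.04 ≈ 124 per arm.

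The allowance of 52 in 300 gives 124 / (1 − 52/300) = 150 per arm. Both figures match the article, and neither depends on the BSFS indicator.

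**Reading 1: change in stool type (per stool or per day).** Success means start minus end ≥ 3.

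| Start | End | Fall | 3-point rule | Out of types 6/7? |
|---|---|---|---|---|
| 7 | 5 | 2 | not met | yes |
| 7 | 4 | 3 | met | yes |
| 7 | 1 | 6 | met | yes |
| 6 | 5 | 1 | not met | yes |
| 6 | 4 | 2 | not met | yes |
| 6 | 3 | 3 | met | yes |
| 6 | 2 | 4 | met | yes |
| 6 | 1 | 5 | met | yes |

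From type 6, the formed and soft stool fails and the hardest stool passes.

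**Comparison with the primary stool criterion.** Take a patient with type 6 every day before treatment and type 4 every day on treatment. Type 6/7 days go from 7 in 7 to 0 in 7, a fall of 100%, which exceeds 50%. If this lasts at least 2 weeks, the primary stool criterion is met. The BSFS fall is 6 − 4 = 2, so the secondary indicator is not met.

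**Reading 2: change in a weekly mean (an assumption; the article names no unit).** With baseline mean m, success needs a final mean ≤ m − 3.

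| Baseline week | Mean | Fall if every day becomes type 4 | Final mean needed |
|---|---|---|---|
| 2 days type 6, 5 days type 4 | 32/7 = 4.57 | 0.57 | ≤ 1.57 |
| 4 days type 6, 3 days type 5 | 39/7 = 5.57 | 1.57 | ≤ 2.57 |
| 7 days type 6 | 6.00 | 2.00 | ≤ 3.00 |
| 7 days type 7 | 7.00 | 3.00 | ≤ 4.00 |

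The first row sits at the entry minimum and is an illustration, not a typical patient. Two results hold generally:

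- If m < 6, the final mean must be below 3, so at least one day must be type 1 or 2.
- To succeed with a final mean of 4, m must be at least 7, which means type 7 on every baseline day.

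**The case against.** The case for leaving the rule alone has several parts.

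- **A stricter secondary threshold may legitimately disagree with the primary.** This is true. A reader might infer that the primary counts any move out of types 6/7 and that the two measures are contradictory as such. The article does not support that, because the primary needs a fall of more than 50% in type 6/7 days, sustained for at least 2 weeks. What stands is narrower: the rule is not just stricter, since it ranks 6 to 1 above 6 to 4.
- **Success without hard stools is possible.** This is correct. Changes from 6 to 3 and from 7 to 4 or 3 all pass on a stool-type reading, so the indicator does not require over-correction on that reading.
- **The primary also credits a move to type 1.** This is correct too. The lack of a check on over-correction is not peculiar to this indicator, and a replacement based only on type 6/7 days would share it and largely duplicate the primary.
- **The unit is a detail for the full protocol.** This is a fair point, and the missing unit is not the complaint. The stated threshold misclassifies 6 to 4 on both readings checked above.
- **The article calls no stool type normal.** This is also true. The judgement that type 4 is a better end point than type 1 rests on the scale's descriptors and on the primary treating fewer type 6/7 days as improvement.
- **The consequence is small.** The indicator is secondary and does not appear in the abstract's list of secondary outcomes. It is applied alike in two blinded arms, so it does not by itself favour either one. This limits the weight of the point but does not make the rule a sound measure of improvement.

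**Conclusion.** The point holds for the stated rule. With no target range or lower limit, a fall of three or more points fails a change from type 6 to type 4 and accepts a fall to type 1 from either type 6 or type 7. A patient with daily type 6 who reaches daily type 4 can meet the primary stool criterion and fail this indicator. This part needs no assumption beyond the scale's own descriptors.

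The weekly-mean results (finish below 3 if the baseline mean is below 6; only daily type 7 can succeed by ending at a mean of 4) depend on a unit that the article does not give.

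A reader might go further and infer that most eligible patients cannot register a benefit on this indicator. The documents do not support that. They give no baseline BSFS distribution and no share of patients starting at type 7, and the entry rule of 2 days is a minimum. The number affected is unknown. The primary outcome and the sample size are untouched, so this is a correction worth making to one secondary endpoint and no threat to the trial's main conclusion.

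**What to change.** Replace the 3-point rule with the change from baseline in the percentage of diary days with stool types 3–5, compared between arms with adjustment for the baseline percentage. Report the percentage of days with types 1–2 separately by arm, so that over-correction is visible. The 3–5 range is a proposal, because the article names no target range; the investigators should confirm it in writing. If the 3-point rule is kept because it is already registered, state its unit and add the measure above as a supplementary analysis, fixed before unblinding.

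The cost is modest. Stool consistency is already recorded daily in the symptom diary, so no new data are needed. The work is extra derivation code and an amendment to one secondary endpoint. Under the article's section on protocol amendments, that means signature by the principal investigator, renewed Ethics Committee approval and sponsor sign-off.
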